#### Clinical Self-Rating Questionnaires

The Symptom Checklist-90-Revised (SCL-90-R) is a 90-item self-report symptom inventory developed by Derogatis (Derogatis and Unger, 2010) in the mid-1970s to measure psychological symptoms and psychological distress. It is designed for use with individuals from the community, as well as with individuals with either medical or psychiatric conditions. The SCL-90-R assesses psychological distress along nine primary symptom dimensions and three summary scores, which are referred to as global scores. The principal symptom dimensions are labeled Somatization (SOM), Obsessive-Compulsive (OBS), Interpersonal Sensitivity (INT), Depression (DEP), Anxiety (ANX), Hostility (HOS), Phobic Anxiety (PHOB), Paranoid Ideation (PAR), and Psychoticism (PSY). The three global measures are the Global Severity Index (GSI), the Positive Symptom Distress Index (PSDI), and the Positive Symptom Total (PST) (Derogatis and Unger, 2010).

The Satisfaction with Life Scale (SWLS) assesses subjective well-being by focusing on global life satisfaction. It does not tap related constructs such as positive affect or loneliness. The SWLS has favorable psychometric properties, including high internal consistency and high temporal reliability. Scores on the SWLS correlate moderately to highly with other measures of subjective well-being and correlate predictably with specific personality characteristics (Diener et al., 1985; Pavot et al., 1991).

The Behavior Rating Inventory of Executive Function–Adult Version (BRIEF-A) is a self-report form designed to be completed by adults 18–90 years of age, including adults with a wide variety of developmental, systemic, neurological, and psychiatric disorders, such as attention disorders, learning disabilities, autism spectrum disorders, traumatic brain injury, multiple sclerosis, depression, mild cognitive impairment, dementia, and schizophrenia. The BRIEF-A is composed of 75 items in nine non-overlapping and theoretically and empirically derived clinical scales that measure various aspects of executive functioning (Gioia et al., 2000; Kessler et al., 2005).

The Adult ADHD Self-Report Scale (ASRS) include 18 questions about the frequency of recent the Diagnostic and Statistical Manual of Mental Disorders (DSM-IV) Criterion A symptoms of adult ADHD. The ASRS screener includes six out of these 18 questions that were selected based on stepwise logistic regression to optimize concordance with the clinical classification. ASRS responses were compared to blind clinical ratings of DSM-IV adult ADHD in a sample of 154 respondents who previously participated in the US National Comorbidity Survey Replication (NCS-R), oversampling those who reported childhood ADHD and adult persistence (Reitan and Wolfson, 2004).

The Alcohol Use Disorders Identification Test (AUDIT) consists of a 10-item Core questionnaire and an 8-item Clinical procedure. AUDIT was designed to identify hazardous drinkers (whose drinking increases their risk of alcohol-related problems, although alcohol-associated harm has not yet occurred); harmful drinkers (who have had recent physical or mental problems related to their drinking, but who are not alcohol-dependent); and people with alcohol dependence (Tombaugh, 2004).

The Drug Use Disorders Identification Test (DUDIT) is an 11-item self-report questionnaire developed to screen individuals for drug problems (Gioia et al., 2000).

The quality register is a national semi-structured interview for the Norwegian healthcare system that is used as a tool for patient feedback and the mapping of patient health, quality of life, employment, housing, and education.

#### Neuropsychological Tests

The Montreal Cognitive Assessment (MoCA) (Voluse et al., 2012) takes approximately 10 min to administer and is designed to detect mild cognitive impairment in elderly participants who score in the normal range on the Mini-Mental Status Examination. The MoCA uses 30 items to assess multiple cognitive domains, including: short-term memory (5 points); visuospatial abilities via clock drawing (3 points), and a cube copying task (1 point); executive functioning via an adaptation of the Trail Making Test Part B (1 point), phonemic fluency (1 point), and verbal abstraction (2 points); attention, concentration, and working memory via target detection (1 point), serial subtraction (3 points), digits forward (1 point), and digits backward (1 point); language via confrontation naming with low-familiarity animals (3 points) and repetition of complex sentences (2 points); and orientation to time and place (6 points) (Voluse et al., 2012). The MoCA is scored by obtaining an item total, and the authors recommend a clinical cutoff score of 26 (Voluse et al., 2012).

The Stroop Color and Word Test (SCWT) is used extensively to assess the ability to control the cognitive interference that occurs when the processing of a specific stimulus feature impedes the simultaneous processing of a second stimulus attribute, which is well known as the Stroop effect. The Stroop test has been used in previous trials on physical exercise and cognition and is a sensitive measure of prefrontally mediated cognitive functions (Bohn et al., 1995; Nasreddine et al., 2005).

The Trail Making Test is a test of visual attention and task switching. It consists of two parts in which the subject must connect a set of 25 dots as quickly and accurately as possible (Golden and Freshwater, 1978). The test provides information about visual search speed, scanning, speed of processing, and mental flexibility, as well as executive functioning (Arnett and Labovitz, 1995; Arbuthnott and Frank, 2000; Martínez et al., 2016; Scarpina and Tagini, 2017).

## Anticipated Results

In this study, we expect the participants in both the control and intervention groups to show progress in physical and mental health after a period of substance abuse. We believe that the data generated in this project will mostly be at the interval or ratio level (whether the rating of perceived exertion is ordinal or interval data will not be discussed here). We will use the mean as a measure of central tendency for the group results for the neurocognitive test, while the reflexes we use frequency and proportions, and the standard deviation to express the spread of results within the group. If useful, the standard error of the mean (SEM) will be used to express the accuracy of the mean value. If the results are highly skewed (skewness > 1.5), we will use a log transformation and geometric mean together with a 95% confidence interval to express central and spread tendencies. To compare results over time from pretest to posttests, and between-group differences, we will use repeated measures ANOVA/*t*-tests with Sidak/Holm *post hoc* tests, where we have collected three or more measurements a linear mixed modeling accounting for the missing data will be used. Group comparisons will be made with an ANOVA/*t*-test for independent groups. If the test of normality should fail (Kolmogorov–Smirnov with Lilliefors correction), the corresponding non-parametric tests will be used, i.e., the Wilcoxon–Mann–Whitney rank sum test for independent *t*-tests and repeated measures ANOVA for ranks (Tukey’s *post hoc* test). Statistical significance will be set at a *p*-value of ≤0.05, and effect sizes will be calculated according to Cohen (1988), with the help of an online effect size calculator (the CEM effect size calculator, Center for Evaluation and Monitoring, Durham University, United Kingdom^1^). An effect size of ≥0.5 will be considered clinically relevant (two-sided). If there is a need for building indexes of different types of scores, *Z*-scores will be used. Based on previously published data on fitness development and depression scores, we should be able to attain statistical power of 0.8 with at least 10 subjects in each of the two groups. Nevertheless, we have set target recruitment at *n* = 30 for each group.

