## Abstract

This proposed study will examine whether structured physical activity reduces the recovery time of cognitive functioning during the early phase of substance use disorder treatment. Addiction or substance dependence is associated with neurobiological changes and cognitive impairment that can affect quality of life and the efficacy of therapy for up to a year after clinical detoxification. The biological, psychological, and social effects of physical exercise have the potential to be a therapeutic approach to increase quality of life and relieve symptoms associated with substance abuse, such as psychosis, depression, and anxiety. There is a dearth of research on physical activity and exercise in clinical substance use disorder patients. This protocol describes a clinical study that will examine cognitive recovery after substance abuse using physical exercise as a treatment intervention. We will use a quasi-experimental longitudinal clinical trial, with a pretest and multiple posttests, on naturally randomized sequential groups. Patients will be consecutively be recruited into the study groups, with a control group that is completed, before its followed by an intervention group, each with 30 patients. Patients will be enrolled 2 weeks after the start of detoxification, at which time all subjects will be inpatients at the Stavanger Salvation Army Treatment Center in the Norwegian specialized healthcare system. Cognition will be evaluated with a comprehensive battery of cognitive tests, including several tests of executive function. Physical fitness will be tested with the Rockport 1-Mile Walk Test, the 30-S Chair Stand Test, the 1-Min Burpee Test at baseline (within the first 2 weeks of admittance) and after 4 weeks. The intervention will be a 30-min workout at 70–90% of maximum heart rate (134–170 bpm), recorded and calculated by a Polar heart rate monitor. The intervention treatment will be administered four times a week for 4 weeks and will consist of high-intensity circuit training, high-intensity interval training, functional movement, and primitive reflex training. We anticipate improvement in both the control and intervention groups, with the exercise intervention group having the greatest increase in recovery of cognitive function because of the combination of functional full body movements and primitive movement training in an intense interval training program.

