1.This study protocol is designed to investigate the impacts of HIIT and HICT combined with functional exercises and primitive reflex training on quality of life and cognitive functioning for patients with SUD. Specifically, the protocol will examine whether structured physical activity improves cognitive functioning for SUD patients relative to that of SUD patients in a control group.2.We will examine whether different intensities of physical activity, such as HIIT/HICT versus other types of physical activity (e.g., hiking) are associated with different cognitive recovery trajectories during the subacute phase of SUD treatment.

This research protocol has several possible applications. First, it will enable future studies to reproduce the exercise protocol and increase the knowledge base on SUD and the effects of exercise. One of the more significant problems in the exercise literature is the inadequate description of exercise, such as the dose, intensity, and how exercises are implemented in studies, which limits reproducibility. This protocol and training regime would serve as a base for comparisons with other workout routines, types of exercises, and duration of exercises. Because this exercise regime will be compared with control group activities, it will be validated as having positive or negative effects for SUD patients in a subacute clinical setting.

Second, because there are so few studies on exercise and substance abuse, a protocol will make it easier to reproduce and increase the number of studies with identical exercise regimes by using this protocol as a guide. This would facilitate comparisons between studies and allow for systematic reviews and meta-analyses.

Third, if this protocol leads to an effective intervention which improves the participants’ cognitive functioning and quality of life, the training regime would be inexpensive and easy to implement in a clinical setting, as there is no need for specialized equipment or extensive staff training.

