1.Baseline testing. The physical and neuropsychological testing will be conducted within 2 weeks of admittance to the Salvation Army Treatment Center.2.The researchers will not conduct randomization, as there is natural allocation as a result of the SUD treatment allocation system, which will be continuous throughout the study.3.The control group is completed first. Structure is changed in the clinic and intervention group is started up after the last control patient has left the clinic.4.The intervention will consist of the physical exercise protocol, which will be conducted for 4 weeks.5.The final tests of physical function will be conducted the week after the exercise protocol is completed. The prospective follow-up will consist of cognitive testing carried out at 3, 6, 9, and 12 months after the baseline test.6.Discontinuation: Patients that don’t follow the protocol or don’t follow the TAU of the Facility will be discontinued. If they don’t complete the follow up test with in the allocated time line or neglect to perform the test they will be discontinued (Figure 1).

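### The only power statement rests on fitness and depression although the aim is cognition, and no cognitive outcome or contrast is primary among many outcomes tested without control across them

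*Protocol article*

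**What the plan says.** - **Aim.** The Abstract opens with recovery of cognitive functioning. The Introduction states the interest as effects "on quality of life and cognitive functioning for patients with SUD", then narrows to cognition relative to control.
- **Outcomes.** Testing Procedures lists three fitness tests. Neuropsychological Testing lists six self-rating scales (SCL-90-R, SWLS, BRIEF-A, ASRS, AUDIT, DUDIT), a quality-register interview and three cognitive tests (MoCA, Stroop, Trail Making). None is called primary.
- **Visits.** Stepwise Procedures plans "cognitive testing carried out at 3, 6, 9, and 12 months after the baseline test". With baseline that makes five measurements, and no visit is singled out.
- **Power.** Anticipated Results claims power of 0.8 with 10 or more per group. The basis it offers for this reads "Based on previously published data on fitness development and depression scores". It gives no effect size or standard deviation. The recruitment target is two groups, "each with 30 patients".
- **Tests.** The same section says "Statistical significance will be set at a" p-value of at most 0.05. It names Sidak/Holm post hoc tests for the repeated-measures comparisons, a linear mixed model where there are three or more measurements, and, in a separate sentence, ANOVA or t-tests for independent groups. Z-score indexes may be built if needed. A standardised effect of 0.5 is the threshold for clinical relevance.

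**The concern.** The sample-size argument and the research question concern different outcomes. A power claim for fitness or depression says nothing about whether 30 per group can answer a question about cognition, and no cognitive effect size appears anywhere.

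Nor does the article say which cognitive result decides the trial. Three tests, two of them with several natural scores, and four follow-up visits all stand level with each other and with the self-ratings. As written, a single significant score could be offered as the trial's answer. The article describes the registration as retrospective, so it shows no prior public commitment that would narrow the choice.

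**Working it through.** **1. What the stated power implies.** The claim cannot be reproduced, because no effect size is given, so it is solved backwards. For two independent groups of n, two-sided 0.05, power 0.80:

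d = (1.960 + 0.842) × √(2/n) = 2.802 × √(2/10) = 1.25 (normal approximation).

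The noncentral t gives 1.32. A one-sided test would need 1.11 (normal) or 1.16 (t). A paired, within-group comparison of 10 would need 1.00. Every reading is at least twice the article's threshold of 0.5.

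**2. Power at the article's own threshold, d = 0.5.** Power ≈ Φ(d√(n/2) − 1.960):

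- n = 10: Φ(1.118 − 1.960) = 20%; with the t distribution 19%.
- n = 30: Φ(1.936 − 1.960) = 49%; with the t distribution 48%.
- n for 80%: 2 × (2.802/0.5)² = 62.8, so 63 per group; with the t distribution 64.
- Smallest d with 80% power at n = 30 (t): 0.74.

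These figures are for an unadjusted comparison without dropout. Adjusting for baseline with correlation r multiplies the variance by (1 − r²). The article gives no r, so a range is assumed (normal approximation for n and power):

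| r | n per group for 80% at d = 0.5 | Power at 30 per group | Detectable d at 30 per group, 0.74 × √(1 − r²) |
|---|---|---|---|
| 0.5 | 48 | 61% | 0.64 |
| 0.7 | 33 | 77% | 0.53 |
| 0.8 | 23 | 90% | 0.44 |

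**3. Error across outcomes.** Assume the mixed model or Sidak/Holm fully controls the visits, so that each instrument contributes one two-sided test at 0.05. For k independent tests, the chance of at least one false positive is 1 − 0.95^k. For correlated outcomes it was simulated with equicorrelated normal statistics (200,000 draws), at assumed correlations of 0.3 to 0.7.

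| Family | k | Independent | Correlation 0.3 | Correlation 0.7 |
|---|---|---|---|---|
| Cognitive tests | 3 | 14% | 14% | 11% |
| Cognitive plus self-rating scales | 9 | 37% | 32% | 20% |
| The above plus fitness | 12 | 46% | 40% | 23% |

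One score per instrument is a lenient count: SCL-90-R alone yields twelve scores (nine dimensions, three global) and BRIEF-A nine scales.

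**4. If visits are not controlled.** The three cognitive tests at four visits make 12 tests: 46% if independent, and 23–39% under assumed correlations of 0.3–0.7 between outcomes and 0.5–0.8 between visits.

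**The case against.** A reader might infer that every score at every visit is tested separately at 0.05, so that a chance positive is likely. The article does not support that. Cognition has five measurements and therefore falls under the mixed model, and Sidak/Holm is attached to the comparisons over time and between groups. Both can limit error across visits within one outcome. Counts that run every questionnaire through all four visits also go beyond the text: follow-up is described only as cognitive testing, and repetition of the self-ratings is not stated. With visits controlled, every figure in the table stays below one half.

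Direction matters too. A claim of benefit needs a favourable result, so the relevant rate per test is 0.025. If independent, that gives 1 − 0.975³ = 7% for three tests, 1 − 0.975⁹ = 20% for nine and 1 − 0.975¹² = 26% for twelve. These still exceed the 2.5% that one test would carry.

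Cognition is also central throughout the article, so the targets are less scattered than the list of instruments suggests; it is the power sentence that departs from them. Finally, the full protocol, the analysis plan and the registry entry are not shown and may rank the outcomes. That is fair for a missing hierarchy taken alone. It does not repair a power statement that, in the article's own words, rests on outcomes other than the aim.

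Two further inferences should be resisted. The 10-per-group claim is not shown to be false: fitness may well respond with an effect above 1. And 30 per group is not shown to be too few for cognition: with a baseline correlation of 0.7–0.8 and no dropout, power at d = 0.5 would be 77–90%.

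**Conclusion.** The point holds in a limited form. The power statement does not bear on the cognitive aim; no cognitive outcome or contrast is primary; and no error control across outcomes is stated. The scope of Sidak/Holm is unclear, because separate independent-group tests are also planned.

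Error is inflated well above 5% even on the favourable assumption that visits are fully controlled, and more so if visits or subscales are tested unadjusted. This rests on one score per instrument and on the assumed correlations, since the article gives none.

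On power, the effect implied by 10 per group is about 2.6 times the relevance threshold (1.32/0.5). Whether 30 per group suffices cannot be judged until the outcome, its analysis and its baseline correlation are named. The change deserves to be made because it alters what the trial can conclude.

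**What to change.** 1. Name one primary cognitive outcome. A Z-score composite of Stroop, Trail Making and MoCA is one reasonable choice, which the article's provision for Z-score indexes already allows.
2. Name one primary contrast from the planned mixed model, tested at two-sided 0.05: either the group difference at one stated visit or the group-by-time effect. The second may fit the stated interest in recovery time and trajectories better.
3. Replace the power sentence with the power or detectable effect for that outcome at 30 per group: for a group difference at one visit, about d = 0.74 for 80% power unadjusted, smaller with baseline adjustment at a stated correlation, and with an allowance for dropout.
4. State which comparisons Sidak/Holm covers and how the separate independent-group tests relate to the mixed model.
5. Apply Holm to a short list of secondary outcomes including quality of life, and label the rest exploratory.

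The cost is wording in the protocol, analysis plan and registry entry, with no new patients or data. The downside is that isolated significant scores can no longer be claimed as confirmatory, and the stated power becomes less favourable.

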### Limitations of the Study

Because the intervention and control groups will be run consecutively rather than concurrently, there is the potential for non-equivalent time periods to create bias. However, we chose this approach because previous studies had suffered recruitment failures and high dropout rates. The length of the proposed study is not fixed, and because of our funding and support, this study can continue until the quota for participants is met.

This study is designed to accommodate clinical realities. Thus, different SUD groups are not fractionated during treatment, and the project protocol does not divide different groups of SUD after clinical classification. This may create some problems with the results from baseline because of various issues with the abuse of different drugs and possible side effects that might affect the test results differently. We will account for this Statistically.

Finally, the patient population will be recruited straight out of a detoxification clinic, which will most likely influence the test results. However, this may actually be an advantage, because having access to patients so quickly after controlled, medically supervised detoxification may give us a more accurate picture of their mental status when the patients are at their lowest point in their recovery trajectories.

The Norwegian Ministry of Health and Social Affairs and the Salvation Army of Norway have provided financial support for this study.

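### The 0.5 effect-size rule for clinical relevance acts on a point estimate tied to neither a baseline-using analysis nor an interval, in a sequential non-randomised comparison

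*Protocol article*

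**What the plan says.** All of the relevant analysis text is in the protocol article, Anticipated Results.

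- **Effect size:** "effect sizes will be calculated according to Cohen (1988), with the help of an online effect size calculator". No input is named: it could be post-test scores, change scores or a model estimate.
- **Rule:** "An effect size of ≥0.5 will be considered clinically relevant (two-sided"). One cut-off serves every outcome, and no interval is attached to it.
- **Significance:** set separately: "Statistical significance will be set at a *p*-value of ≤0.05".
- **Analyses:** pretest-to-posttest repeated measures ANOVA or t-tests; a linear mixed model that handles missing data where there are at least three measurements; and, for group comparisons, an independent-groups ANOVA or t-test. No baseline covariate is named for any of them.
- **Size:** "we have set target recruitment at *n* = 30 for each group".

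Under Stepwise Procedures, the control cohort is finished before the intervention cohort starts, and the clinic's structure changes in between. Limitations of the Study concedes that the different time periods may bias the comparison. It promises a statistical allowance for drug type but gives no method.

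**The concern.** The rule turns a number into a conclusion, so it matters which number is used. In a randomised trial, an effect size from unadjusted post-test means would be noisy but unbiased. Here the cohorts are consecutive, and nothing ensures that they start at the same level. A standardised difference that ignores the pretest attributes part of any starting difference to the exercise programme.

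Because the input is left open, the same outcome could pass 0.5 on one contrast and miss it on another. The relevance label could then disagree with the planned model for that outcome. Judging relevance on the point estimate alone also hides how imprecise it is at this sample size.

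**Working it through.** **1. The plan's own figure.** The article states: "we should be able to attain statistical power of 0.8 with at least 10 subjects in each of the two groups". It gives no effect size or SD, so the figure cannot be reproduced; only the implied effect can be found. Two-sided at 0.05, d = (1.960 + 0.842) × √(2/10) = 1.25, or 1.32 with the t distribution. That is more than twice the relevance threshold. It says nothing about how the 0.5 rule behaves, so the remaining steps use the target of 30 per group.

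**2. Precision at the threshold.** SE(d) = √(2/n + d²/(4n)). With n = 30 and d = 0.5: √(0.06667 + 0.00208) = 0.262. The 95% CI is 0.5 ± 1.96 × 0.262, or -0.01 to 1.01. With 20 completers per group (an assumption; the article gives no completer number), SE = 0.321 and the CI is -0.13 to 1.13.

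**3. No true effect and no bias, n = 30.** An observed d of 0.5 corresponds to t = 0.5 × √(30/2) = 1.936 on 58 df, so P(|d| ≥ 0.5) = 0.058. The smallest d significant at 0.05 is 2.002 × √(2/30) = 0.517.

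**4. Carry-over of a baseline imbalance b.** Assume equal SDs, and cohorts that differ at the pretest but would otherwise regress to a common mean. With pre-post correlation r, the expected shift is:

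- post-test contrast: r × b
- change-score contrast: (r - 1) × b
- baseline-adjusted contrast: 0

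The article gives no r, so a range is shown for b = 0.3 SD.

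| Assumed r | Post-test d | Change-score d |
|---|---|---|
| 0.5 | +0.15 | -0.15 |
| 0.7 | +0.21 | -0.09 |
| 0.9 | +0.27 | -0.03 |

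Whatever r is, the post-test and change-score contrasts differ by b itself, here 0.30. That is large against a threshold of 0.5.

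**5. A cohort difference that persists to the post-test, no treatment effect, n = 30.** Under these assumptions d × √(n/2) follows a noncentral t on 58 df with noncentrality δ × √15. P(d ≥ 0.5 in the direction of the difference) is:

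| Assumed δ (SD) | Noncentrality | Probability |
|---|---|---|
| 0.2 | 0.775 | 0.128 |
| 0.3 | 1.162 | 0.225 |
| 0.4 | 1.549 | 0.355 |
| 0.5 | 1.936 | 0.503 |

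With no difference the one-direction figure is 0.029, half of 0.058. If the same 0.3 SD was already visible at the pretest and r = 0.7, baseline adjustment leaves 0.3 - 0.7 × 0.3 = 0.09.

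**The case against.** The strongest reply is that an article condenses the plan. Which contrast is standardised, by which SD and with what interval is usually left to the SAP, and nothing here rules out a model-based effect size. The same paragraph plans analyses that use the pretest and a mixed model for missing data, Stepwise Procedures plans intention-to-treat and per-protocol analyses, and a period limitation is disclosed. Significance is a separate criterion, and no success claim or stopping rule depends on the 0.5 label. At 30 per group the rule almost coincides with the test: relevant but non-significant covers only 0.50 to 0.517, and the null rate is 5.8% against 5%.

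Much of this stands. It removes the argument that the rule is badly miscalibrated at the planned size. It also rules out three stronger readings that a reader might infer:

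- **That the plan specifies a raw effect size.** It does not; the input is unspecified. Using the calculator is not a fault in itself.
- **That dropout alone would produce a relevant result.** Losing the lowest-scoring 30% of one group only, and comparing completers, shifts that group's mean by φ(-0.524)/0.70 = 0.50 SD. Nothing in the article points to so extreme a pattern. The remark that "previous studies had suffered recruitment failures and high dropout rates" concerns earlier studies and explains the choice of sequential groups; it is not this trial's expected loss.
- **That a modest imbalance alone reaches the threshold.** A 0.3 SD imbalance adds 0.21. At r = 0.7 the imbalance would have to be 0.5/0.7 = 0.71 SD.

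The condensation argument does not dispose of the point. The article does not stay silent on relevance: it fixes a cut-off on an effect size and connects it to neither a baseline-using analysis nor an interval. The mixed model is not promised for outcomes measured only twice, such as the fitness tests, and the disclosed period bias is not linked to the rule.

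**Conclusion.** The point holds in a limited form. The protocol sets a relevance threshold on a point estimate whose contrast is undefined, in a design where the contrast matters.

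The size depends on assumptions that the article neither states nor excludes. If post-test means and SDs are used, a 0.3 SD baseline imbalance adds 0.15 to 0.27 for r between 0.5 and 0.9, and 0.21 at r = 0.7. If a cohort difference of 0.2 to 0.5 SD persists to the post-test with no treatment effect, the label is given in that direction with probability 0.13 to 0.50 at 30 per group. The interval at d = 0.5, from -0.01 to 1.01, needs no assumption about bias, only that 30 per group are analysed; it widens if fewer are.

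This is an improvement available at no cost. It is not an error that invalidates the planned analysis.

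**What to change.** Define the effect size as the baseline-adjusted between-group difference divided by the pooled baseline SD.

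- **Three or more measurements:** take the group contrast from the mixed model already planned, with the pretest in the model and the visit named.
- **Two measurements:** take it from ANCOVA on the pretest.
- **Reporting:** give the 95% CI with every effect size, apply the 0.5 threshold to this estimate, and read the label together with the interval. A calculator may still do the arithmetic if it is fed this contrast.

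The cost is a few sentences in the analysis section or SAP; no patients, visits or data are added. Adjustment removes only what the pretest shows. Period effects that arise after baseline remain, so the acknowledged limitation should be repeated wherever the relevance label is used.

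### The claim of 0.8 power with 10 per group rests on fitness and depression data and does not hold for the cognitive aim at the plan's own relevance threshold of 0.5

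*Protocol article*

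**What the plan says.** Everything on power and effect size stands in one paragraph of the protocol article, under Anticipated Results.

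- Basis: "Based on previously published data on fitness development and depression scores".
- Claim: "we should be able to attain statistical power of 0.8 with at least 10 subjects in each of the two groups". No effect size, standard deviation or correlation accompanies it.
- Target: "we have set target recruitment at *n* = 30 for each group".
- Relevance: "An effect size of ≥0.5 will be considered clinically relevant (two-sided". This is the only effect size in the article.
- Significance: "Statistical significance will be set at a *p*-value of ≤0.05".
- Analysis: "Group comparisons will be made with an ANOVA/*t*-test for independent groups". For comparisons over time, "we will use repeated measures ANOVA/*t*-tests with Sidak/Holm *post hoc* tests", with a linear mixed model where there are three or more measurements.

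The Abstract and the numbered aims at the end of the Introduction make cognitive functioning relative to control the study question. Stepwise Procedures schedules cognitive testing at 3, 6, 9 and 12 months after baseline, which makes five measurements.

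**The concern.** The power statement concerns outcomes other than the one the study is about. An effect of exercise on fitness or depression cannot simply be carried over to cognition, least of all against a control group that also takes daily hikes and a longer weekly hike (Control Group section) and is itself expected to improve.

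The claim also sits beside a relevance threshold that it does not serve: 10 per group gives 80% power only for a difference more than two and a half times as large. A reader who takes the sentence at face value could treat a non-significant cognitive result as evidence against an effect worth having, when some of the listed analyses would often miss one.

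**Working it through.** **Inputs from the article.** Two-sided significance level 0.05; standardised difference d = 0.5, so SD = 1; 10 or 30 per group; independent-groups t-test, or a mixed model for three or more measurements. **Assumed, because the article gives none:** the correlation r between measurements, the pattern of the effect over time, and the dropout rate.

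**1. The plan's own figure.** It cannot be reproduced, because the effect size behind it is not given. Working backwards with the noncentral t distribution (noncentrality d·√(n/2), 2n − 2 degrees of freedom), 80% power at n = 10 requires d = 1.32. Against the stated threshold, 1.32/0.5 = 2.6.

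**2. Ten per group at d = 0.5.**
- Independent t-test: noncentrality 0.5·√5 = 1.118, power 18.5%. A one-sided test would give 28.5%.
- Baseline adjustment at one visit: effective d = 0.5/√(1 − r²). Reaching 80% needs r of about 0.93.
- Baseline-adjusted mean of four follow-ups, with equal correlation r between all visits and a constant effect: residual variance V = (1 + 3r)/4 − r², effective d = 0.5/√V. At r = 0.3, V = 0.385, effective d = 0.81, power 40%. At r = 0.5, V = 0.375, effective d = 0.82, power 41%. At r = 0.7, V = 0.285, effective d = 0.94, power 51%.

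None of these comes near 0.8 at plausible correlations. For the unadjusted t-test, 80% power at d = 0.5 needs 64 per group.

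**3. Thirty per group, by analysis (no dropout).** The unadjusted detectable difference at 80% power is 0.736 SD. It is multiplied by √(1 − r²) for one adjusted visit and by √V for the four-visit mean.

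| Analysis | Power at d = 0.5 | Difference detectable with 80% power |
|---|---|---|
| Unadjusted t-test, one visit | 48% | 0.74 SD |
| Baseline-adjusted, one visit, r = 0.5 | 59% | 0.736 × 0.866 = 0.64 SD |
| Baseline-adjusted, one visit, r = 0.7 | 76% | 0.736 × 0.714 = 0.53 SD |
| Adjusted four-visit mean, r = 0.5 | 87% | 0.736 × 0.612 = 0.45 SD |
| Adjusted four-visit mean, r = 0.7 | 95% | 0.736 × 0.534 = 0.39 SD |

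**4. Sensitivity to loss.** With an assumed 30% loss (21 per group), the unadjusted t-test has 35% power at d = 0.5. The four-visit mean has 73% at r = 0.5 and 84% at r = 0.7.

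**5. Relevance rule.** At 30 per group the smallest observed difference that reaches p = 0.05 is t(0.975, 58)·√(2/30) = 0.517 SD for the unadjusted t-test. It is 0.45 to 0.37 SD with one-visit adjustment at r = 0.5 to 0.7, and about 0.32 to 0.28 SD for the four-visit mean.

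**The case against.** Three stronger readings are tempting, and the article supports none of them.

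**That the 0.8 is an arithmetic error.** The article attributes the figure to published fitness and depression data, not to d = 0.5, and a relevance threshold need not be the planning effect. Ten per group is consistent with a difference of about 1.3, and nothing in the article shows that the cited data lacked one. The derivation may also stand in a fuller document. What remains is that the printed sentence offers no support for the cognitive aim.

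**That the trial is underpowered even at 30 per group.** The 48% belongs to an unadjusted comparison at a single visit. Cognition is measured five times, and the article names a mixed model for three or more measurements. Under the assumptions above, that model exceeds 80% power at d = 0.5 with 30 per group. The objection stands on this point, with one limit: the correlation and effect pattern are assumptions, and dropout, a single-visit comparison or a group-by-time contrast would give less. The article mentions high dropout in previous studies but gives no rate for this one.

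**That every significant result would automatically count as clinically relevant.** This is true only of the unadjusted t-test at 30 per group, where the critical difference of 0.517 exceeds 0.5. In the adjusted and longitudinal analyses a significant result can fall below 0.5, so there the threshold does add information.

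Nor does the article call 30 per group ample. It says only "Nevertheless, we have set target recruitment at" that number.

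**Conclusion.** The concern holds in limited form. The 10-per-group statement is not supported for the study's own question: its basis is not cognitive, its effect size is not stated, and at the article's own threshold of 0.5 the power is 18.5% by t-test and about 40% to 51% by the most favourable analysis examined at r = 0.3 to 0.7. That conclusion does not depend on which listed analysis is used.

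The position at 30 per group does depend on it. Power at d = 0.5 ranges from 48% (one visit, unadjusted) to 95% (four-visit mean, r = 0.7). The upper figures rest on equal correlations between visits, a constant effect and no dropout, none of which the article states. Adequacy at 30 per group is therefore neither shown nor refuted.

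**What to change.** 1. Delete the 10-per-group claim as support for the cognitive question, or confine it to fitness and depression and give the effect size behind it.
2. State power for cognition at 30 per group by analysis, with the assumptions named. For example: a single-visit unadjusted t-test has 48% power for 0.5 SD and 80% power for 0.74 SD; baseline adjustment at one visit with an assumed correlation of 0.5 to 0.7 detects 0.64 to 0.53 SD; the mixed model, for a constant effect averaged over four follow-ups with equal correlations and no dropout, detects about 0.45 to 0.39 SD at the same correlations. Add that dropout, a single visit or a group-by-time contrast is less favourable.
3. Judge clinical relevance from the 95% confidence interval against 0.5, not from the point estimate alone, and call a non-significant result whose interval includes 0.5 inconclusive.

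The cost is wording only. Recruitment, visits and tests do not change and no extra patients are needed. The downside is a less favourable stated power.
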